## Synopsis

|                                     |                                                                                                                                                                                                                                                                                                                                                                                                                                                                                                                                                                                                                                                                                                                                                                                                                                                                                                                                                                                    |
|-------------------------------------|------------------------------------------------------------------------------------------------------------------------------------------------------------------------------------------------------------------------------------------------------------------------------------------------------------------------------------------------------------------------------------------------------------------------------------------------------------------------------------------------------------------------------------------------------------------------------------------------------------------------------------------------------------------------------------------------------------------------------------------------------------------------------------------------------------------------------------------------------------------------------------------------------------------------------------------------------------------------------------|
| Title:                              | IMPact of donor heart function on Recipient Outcomes - a prospectiVE study to increase the utilization of Donor HEARTs                                                                                                                                                                                                                                                                                                                                                                                                                                                                                                                                                                                                                                                                                                                                                                                                                                                             |
| Short background/Rationale/Purpose: | Severe heart failure is a diagnosis with a very poor prognosis. Heart transplantation is the best treatment for terminal heart failure but this type of treatment is limited by the number of available organs. About 20-25% of possible donor hearts are not considered for transplantation because they have some form of functional impairment. The functional impairment affecting organ donors is, however, usually reversible. A number of retrospective studies show that cardiac function recovers and recipients of hearts with dysfunction do not have worse outcomes compared to recipients of hearts with perfect cardiac function. However, there are no prospective studies on whether the functional impairment of the donor heart is of significance for the recipient. With a systematic and simple investigation of the heart, it should be possible to identify the hearts that are safe to transplant. This will thus increase the number of available donors. |
| Study objectives:                   | The objective of the study is to increase the number of available heart donors, which in turn will increase the number of heart transplantations.                                                                                                                                                                                                                                                                                                                                                                                                                                                                                                                                                                                                                                                                                                                                                                                                                                  |
| Study design:                       | Prospective, non-randomized multicenter study                                                                                                                                                                                                                                                                                                                                                                                                                                                                                                                                                                                                                                                                                                                                                                                                                                                                                                                                      |
| Study population:                   | Patients who are planned to undergo heart transplantation                                                                                                                                                                                                                                                                                                                                                                                                                                                                                                                                                                                                                                                                                                                                                                                                                                                                                                                          |
| Number of subjects:                 | A total of 445 transplanted patients will be included, of which at least 89 patients have received a heart with impaired function.                                                                                                                                                                                                                                                                                                                                                                                                                                                                                                                                                                                                                                                                                                                                                                                                                                                 |
| Inclusion criteria:                 | Patients who are accepted for heart transplantation at participating centers.

Aged 18 years or older

The patient must have provided informed consent                                                                                                                                                                                                                                                                                                                                                                                                                                                                                                                                                                                                                                                                                                                                                                                                                 |
| Exclusion criteria:                 | Mental inability, reluctance or language difficulties that result in difficulty understanding the meaning of study participation.                                                                                                                                                                                                                                                                                                                                                                                                                                                                                                                                                                                                                                                                                                                                                                                                                                                  |

|                 |                                                                                                                                                                                                                                                                                                         |
|-----------------|---------------------------------------------------------------------------------------------------------------------------------------------------------------------------------------------------------------------------------------------------------------------------------------------------------|
|                 | Another study, where the patient is included, which is not considered compatible with the current study.                                                                                                                                                                                                |
| Study outcomes: | 
Primary variable: Death, retransplantation or need of mechanical assist one year after the heart transplantation.
 
Secondary variable: Left-ventricular moderate or severe primary graft dysfunction
 
The study has several secondary objectives that are presented in the protocol.
 |
| Study period:   | Q2 2020 – Q2 2027                                                                                                                                                                                                                                                                                       |

## 1. Background and rationale

Severe heart failure is a diagnosis with a very poor prognosis with a 2-year mortality rate is over 50%, which exceeds many cancer diagnoses. Despite advances in pharmacological treatment and mechanical pumps, heart transplantation is considered to be the best treatment for terminal heart failure. However, heart transplantation as a treatment for terminal heart failure is limited by the number of available organs. If more organs were available, more patients would be transplanted. It is therefore of the utmost importance that every heart that can be successfully transplanted is utilized.

According to current recommendations, a heart should be in near perfect condition to be considered for transplantation. For a donor heart to be transplanted, it should not exhibit:

- More than mild-to-moderate cardiac impairment (EF < 40%)
- Regional wall motion abnormalities
- Need for excessive inotropic support (dobutamine >20µg/kg/minute)
- Intractable ventricular arrhythmias.

However, cardiac dysfunction in organ donors is usually secondary to the disease that led to brain death and is generally reversible, i.e., there is nothing wrong with the heart itself but it has been exposed to an unfavorable environment that temporarily affects its function. A common cause of cardiac dysfunction in organ donors is stress-induced cardiomyopathy/Takotsubo cardiomyopathy. Stress-induced cardiomyopathy is a relatively newly described acute cardiac syndrome in which the heart develops regional wall motion abnormalities caused by severe catecholamine stimulation of the myocardium. In organ donors, a strong catecholamine storm is observed with brain herniation and the development of brain death, which can trigger stress-induced cardiomyopathy. This type of change is seen in 20-25% of potential organ donors. One of the most important characteristics of stress-induced cardiomyopathy is its rapid recovery, however, and cardiac function is usually normalized within a few hours or days. This is not only seen as a functional recovery, but also a structural and biochemical recovery of the heart. In addition to organ donors with intracranial events, stress-induced cardiomyopathy is also seen in patients with hypoxic/anoxic brain injuries as a result of hypoxic cardiac arrest, and even in these cases, cardiac events are temporary.

There are potentially differential diagnoses for stress-induced cardiomyopathy in potential donors. The most important is ischemic heart disease which can quickly and relatively easily be diagnosed with coronary angiography. Coronary angiography is performed today on approximately one-third of potential donors and then primarily on donors with a risk profile for coronary artery disease. Another different diagnosis is myocarditis, which does not have the same reversibility as stress-induced cardiomyopathy and usually have a different echocardiographic pattern.

In the transplant society, it is debated whether a heart with a mild/moderate impaired function can be suitable for transplantation. According to previous recommendations, which have been in place for over 10 years, a heart must be in nearly perfect condition to be considered for transplantation. These guidelines lacked scientific evidence but have gained significant acceptance, leading to caution in transplanting such hearts. In a survey of American thoracic surgeons, reduced ejection fraction and regional hypokinesia were ranked as the most important factors for not accepting a heart. Furthermore, these were also identified as the primary reasons for rejecting a heart for transplantation.

There is a number of retrospective studies that show that the outcome is not worse for patients who have been transplanted with hearts that have/have had dysfunction. The main studies are presented below:

- A study based on material from the USA (UNOS database) in which patients who received a heart with ejection fraction <50% (n=740) were identified and compared with recipients of hearts with normal function (n=30253). No difference in mortality at one year after transplantation was observed between the groups.
- A study based on the same material showed that long-term survival was not inferior for recipients of hearts with ejection fraction <50%. Cardiac function was also the same for recipients of hearts with normal function and impaired function one year after transplantation.
- In a study based on the same database (UNOS database) 472 recipients who received a heart with improved function, defined as EF≤40% at one examination and EF≥50% at a follow-up examination, were identified. The control group were recipients of hearts with normal function EF≥55%. There was no difference in mortality, primary graft failure, allograft vasculopathy between the groups, also when propensity score matching was applied.
- A study based on other material from the California Transplant Donor Network reported data where low ejection fraction (EF<50%, number of patients not reported) or regional hypokinesia (n=197) did not affect outcome.
- An older study based on material from the USA showed that regional hypokinesia has no bearing on recipients' mortality. The number of patients with regional hypokinesia was not reported but 1719 patients were included in the study.
- A study from Transplantation Centre, Sahlgrenska, analyzed donors and recipients during a 10-year period. In total, 641 donors were included in the analyses and 155 (24%) of the donors had cardiac dysfunction. Recipients of hearts with dysfunction (n=42) did not have a higher risk of adverse outcomes (death, retransplantation) compared to recipients of hearts with normal function. Short-term outcomes (intensive care unit (ICU) care time, advanced hemodynamic support, postoperative dialysis, rejection) did not differ between the groups. Cardiac function was rapidly recovered in the recipients and both groups had the same ejection fraction already a few days after transplantation.

These studies are the foundation for recently published guidelines regarding which hearts can be considered for transplantation. They suggest that hearts with initially impaired function should be further evaluated, and those that demonstrate functional improvement could be considered for transplantation. However, the level of evidence is low, and the strength of recommendation is moderate (Level of Evidence: C, Level of Recommendation II). There is a lack of prospective studies on the transplantation of hearts with impaired function, which contributes to the low level of evidence and the fact that clinical practice has not changed

In Sweden, there are many years of experience of handling hearts with impaired function. This clinical experience suggests that it is not associated with an increased risk of complications. The study referred to above confirm this experience.

In summary, there is a potential to increase the number of heart donors, and thus the number of heart transplantations, if the heart donors with reversible dysfunction are utilized. This study aims to prospectively investigate the cardiac function of donors and evaluate if it is of significance to the outcome of the recipient. The study sets guidelines for investigative procedures as well as which hearts should be transplanted, based on previous retrospective studies. We expect that the recipients' outcome will not be affected by the cardiac function of the donor, provided the study's recommendations are followed. Our data shows that approximately every fourth potential heart donor suffers from functional impairment. This is in line with other studies that observed that about 20% of hearts are refused due to affected function. We estimate that a systematic utilization of these hearts can increase the number of transplantations by 20-30%.

## 2. Risk-benefit evaluation

Today, patients are transplanted with donor hearts with impaired function. In the vast majority of cases, such transplantations occur according to the recommendations given in this study (section 5.1). In retrospective data, these patients do not have worse outcomes in the short- or long-term, also in adjusted data. However, in retrospective studies we do not have control of all covariates and there may be factors that the responsible surgeon took into account which could not be measured. Thus, there is a conceivable risk that patients have an increased risk for complications, if the utilization of such hearts would be more liberal.

The overall benefit of utilizing donor hearts with impaired function is the recipient's shorter time waiting for an organ. For the recipient, this means a shorter time on the waiting list. While waiting for transplantation it is not uncommon that cardiac function deteriorates. The patient might be in need of mechanical assist and in worst case, the patient dies. In addition to the reduction of these risks, the patient's time with a disabling disease is decreased.

The study will continuously evaluate the results to find an increased risks for the group who has received a heart with impaired function. In such cases, the study will be prematurely terminated.

From a larger perspective, more available heart donors will allow patients to be more liberally accepted for transplantation. In the long-term, we hope that this can change the guidelines for which patients are relevant for transplantation. Our hope is also that fewer patients will need mechanical assist, a treatment that is expensive and limits daily activities.

This study will not expose heart recipients to any examinations or examinations other than those performed as part of clinical follow-up, which means that there is no additional suffering for the patient in the study follow-up.

Based on ours and others' retrospective data, there is no increased risk from receiving a heart that has impaired function. The guidelines set up in this study are based on studies of 1400 reported patients. Based on the state of knowledge today, we expect that these heart recipients will not have an increased risk for complications or death. The benefit for the patients is that they will receive their transplantation faster, which is a favorable factor. Taken together, we estimate that the potential benefit outweighs possible risks.

### 3. Study objectives

The aim of this study is to increase the number of heart transplantations by increasing the number of available donor heart. We will do this by showing that it is safe to transplant hearts with impaired function, provided that they are investigated and that the functional impairment is within the scope of the study guidelines. The study also aims to facilitate and speed up the investigation of possible heart donors. We will also learn more about cardiac dysfunction in organ donors through access to tissue samples.

We estimate that the number of heart transplantations can increase by 20-30% if these donors can be systematically utilized. In practice, this means that the transplantation queue can be reduced and that patients can more liberally accepted for heart transplantation.

#### 3.1. Primary objective

The primary objective is to investigate whether recipients of donor hearts with regional wall motion abnormalities and/or mild to moderate globally reduced cardiac function have the same outcome as recipients of hearts with normal function.

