## 7.4. Sample size calculations

This is a non-inferiority trial. Power calculations are made based on non-inferiority calculations. Based on our retrospective data, the absence of death/retransplantation within a year was 90%. We have calculated power to exclude a difference in the primary outcome of 10%, which is the benefit that may be relevant since patients can be transplanted earlier and more patients can be transplanted. We expect that 20% of the transplantations will come from hearts with dysfunction. The power calculation says then that we need 445 transplanted hearts and at least 89 transplanted hearts with dysfunction. Since we do not know the exact incidence, outcome, or transplantation frequency of hearts with dysfunction in a prospective cohort, we primarily plan to include 500 heart-transplanted patients in the study.

To be able to answer our specific research questions about the heart donors, we estimate that we need at least 100 donors of hearts with dysfunction to be able to have a representative group. With an estimated incidence of cardiac dysfunction in 25% of the donors, at least 400 possible heart donors are needed in the study. However, the study intends to continue collecting data from all donors until the primary objective is answered.

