## 7.5. Interim analysis (if relevant)

Interim analysis will be performed after 100 patients have been analyzed for the primary outcome and then after every 50 patients who have been analyzed for the

primary outcome. Criteria for stopping the study are a confirmed overrepresentation of primary outcome variables in the group of patients who received a heart from a donor with impaired cardiac function. Overrepresentation must be at least 10 absolute percent in the primary outcome measure as well as show statistical significance ( $p < 0.05$ ) for the study to be terminated. An increased incidence of SAE of at least 20 absolute percent as well as statistical significance ( $p < 0.05$ ) can result in termination of the study.

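### The aim and objective speak of safe transplantation and the same outcome, but success in the section 7.4 design shows only that one-year risk is less than 10 absolute percentage points higher

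*Protocol*

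**What the plan says.** Protocol section 3 gives the aim: "We will do this by showing that it is safe to transplant hearts with impaired function", on condition that the hearts are investigated and the impairment falls within the study's guidelines. Section 3.1 poses the primary question as whether recipients of such hearts "have the same outcome as recipients of hearts with normal function". Neither section mentions a margin.

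Section 7.4 states: "This is a non-inferiority trial". The reference figure is that "the absence of death/retransplantation within a year was 90" per cent. The target is described as follows: "We have calculated power to exclude a difference in the primary outcome of 10%, which is the benefit that may be relevant", because patients can be transplanted earlier and in greater numbers. The result is 445 transplanted patients, at least 89 of them with a dysfunctional heart, and 500 are planned.

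Section 7.2.1 specifies adjusted logistic regression and a p-value threshold of 0.05. It does not mention the 10-point difference.

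**The concern.** The objective and the sample size answer different questions. A non-inferiority trial shows that an excess is smaller than its margin; it does not show equality. The protocol nowhere says what its margin means at its own planning rate, and the section on the primary analysis does not use the margin. If the protocol is followed as written, nothing in it limits the conclusion to the excess that was actually excluded.

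This matters because the study is meant to widen the acceptance of these hearts. Section 2 itself concedes that more liberal use could carry added risk. Someone deciding on acceptance needs to know how large an excess of death, retransplantation or mechanical assist has been ruled out.

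The rationale for the margin does not close the gap. Earlier and more numerous transplantations are benefits that arise before transplantation and partly in other patients. Section 7.1 restricts the primary analysis to those who were transplanted.

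**Working it through.** **Inputs**
- One-year failure 10% in both groups (100% − 90%; section 7.4).
- One dysfunctional heart to four normal hearts (20% share; section 7.4).
- Margin 10 points. Section 7.4 does not label the scale. Absolute points are inferred because they reproduce the sample size, and because the harm rule in section 7.5 uses that scale: "Overrepresentation must be at least 10 absolute percent in the primary outcome measure".
- One-sided 2.5% and 80% power. Section 7.4 states neither; both are inferred from the match below.

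**1. Reproducing the sample size**

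n (smaller group) = (1.96 + 0.8416)² × (0.09 + 0.09/4) / 0.10² = 7.849 × 0.1125 / 0.01 = 88.3, rounded up to 89. The total is 5 × 89 = 445, an exact match.

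Other settings do not match: one-sided 5% with 80% power gives 70/350, one-sided 2.5% with 90% gives 119/595, and one-sided 5% with 90% gives 97/485.

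**2. What the margin means**

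At the planning rate: 10% + 10 points = 20% against 10%, a risk ratio of 2.0 and an odds ratio of (0.20/0.80)/(0.10/0.90) = 2.25.

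The 10% covers death and retransplantation only, while the primary variable in section 3.3 adds mechanical assist. The composite rate is not given. For illustration, an assumed 15% gives 25/15 = 1.67, and an assumed 5% gives 15/5 = 3.0. The 10-point excess is the same in each case.

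**3. Precision when the groups look identical**

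- 89 against 356 at 10%: SE = √[0.09 × (1/89 + 1/356)] = 0.0356, so the 95% half-width is 1.96 × 0.0356 = 7.0 points.
- Observed 9/89 against 36/356 (10.1% in both): the upper limit is +7.0 points, or one extra failure per 1/0.070 ≈ 14 recipients.
- 100 against 400 (the planned 500): SE = 0.0335, half-width 6.6 points.

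**4. Which results would pass a 10-point test (unadjusted Wald limits, 36/356 in the normal group)**

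| Impaired group | Excess | Upper 95% limit | Below 10 points? |
|---|---|---|---|
| 9/89 | 0.0 | 7.0 | yes |
| 11/89 | 2.2 | 9.8 | yes |
| 12/89 | 3.4 | 11.1 | no |

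**5. If non-significance were taken as the answer instead**

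Section 7.2.1 offers only a p-value rule. With true risks of 20% and 10%, a two-sided 5% test at 89/356 has about 71% power, so about 29% of such studies would show no significant difference. An observed 15/89 (16.9%) against 36/356 (10.1%) is non-significant, yet its upper limit is about 15 points. A non-significant difference therefore would not exclude even the 10 points that the trial was sized for.

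**The case against.** Section 3.1 asks a question and does not announce a result, and the safety sentence in section 3 is conditional. Section 7.4 openly gives the non-inferiority design, the reference rate, the difference and a reason for it. The statistical analysis plan, not shown here, may fix the decision rule. All of this is fair, and it makes the problem one of alignment between sections. What stands is that the aim and objective are protocol text: as worded they go beyond section 7.4, and an analysis plan does not rewrite them.

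A reader might infer more, and the documents do not support it:

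- *The margin is concealed, or the result is bound to be reported as equality.* Section 7.4 discloses the margin, and section 12 on publication says nothing about how conclusions will be worded.
- *The trial tolerates exactly a doubling of its primary outcome.* The 10% planning rate leaves out mechanical assist. Also, an observed upper limit may fall below 10 points, as it does in the equal-risk case.
- *The chance of passing with a truly higher risk is a flaw.* It is about 43% at 13% against 10%, and 23% at 15% against 10%. Intermediate values are ordinary for a test with 80% power at no difference and a 2.5% pass rate at the margin.
- *The benefit behind the margin goes unexamined.* Sections 3.2 and 7.1 make time to transplantation and the number of transplantations secondary questions and include patients who were not transplanted. Section 2 also describes a shorter wait for the recipient. The narrower point holds: the primary test does not weigh that benefit against excess failure.

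**Conclusion.** The point holds as a mismatch between sections 3 and 3.1 and section 7.4, left open by section 7.2.1. It is not an arithmetic error, since 445/89 reproduces exactly. Success would establish a one-year excess of less than 10 absolute points, which at the planning rate is up to 20% against 10%. It would not establish the same outcome. Even with equal observed risks of 10%, an excess of about 7 points (6.6 with 500 patients) would remain compatible with the data.

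This rests on an absolute margin and on the inferred error rates. It also uses unadjusted Wald limits, so adjusted limits will differ somewhat. The ratio of 2.0 depends on the death/retransplantation rate and should not be read as the ratio for the composite. The change should be made, but it concerns wording and the decision rule, not the size of the study.

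**What to change.** - **Section 3.1:** state the objective as non-inferiority, meaning that the one-year risk of the primary composite is not more than 10 absolute percentage points higher with impaired hearts. Do not write a fixed 20% against 10% into the objective.
- **Section 3:** limit the safety wording to the excess actually excluded.
- **Section 7.2.1:** state that the primary conclusion rests on the upper limit of the two-sided 95% confidence interval for the adjusted risk difference, compared with 10 points. This can be standardised from the planned logistic model. State that the limit is quoted in the conclusion.
- **Section 7.4:** say that at the planning rate the margin permits a doubling, and that the benefit used to justify it is examined only in secondary analyses and is not weighed in the primary test.

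A supportive tighter threshold such as 5 points is not advised. The protocol gives no basis for it, and at equal risks the power would be only about 29% (0.05/0.0356 − 1.96 ≈ −0.55). Powering for it would take 354/1,770 patients.

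The cost is a protocol amendment and no extra patients or data. The downside is a less favourable stated claim.
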